### Data collection and statistical analysis

For all women who consent to participate, the following data will be collected (i) the number and quality of transferred cleavage and blastocyst stage embryos according to the Gardner grading criteria [17] (ii) pregnancy test result 2 weeks after egg retrieval or 9 days after frozen embryo transfer, (iii) if pregnancy test is positive, we will perform an obstetric transvaginal ultrasound at 7–8 weeks gestational age to confirm ongoing pregnancy and multiplicity, (iv) pregnancy outcome (miscarriage, fetal demise, live birth). These data will be entered electronically into patients’ medical records as part of routine clinical care and collected by the study team for analysis. A password system will be utilized to control access to the study data. A complete backup of the primary database will be performed twice a month. All data reports will be prepared such that no individual participant can be identified.

Both intention-to-treat and per-protocol analyses are noted in the RCT reporting guidelines (CONSORT) as valid approaches. For this study, we will perform an intention-to-treat analysis because it is the gold standard for RCTs, even with crossover, withdraw and loss to follow-up. We also will perform a per-protocol analysis as it is a valid statistical approach and will serve as a sensitivity analysis. Descriptive data will be presented as proportion, mean with standard deviation or median with interquartile range. Comparisons will be made using Chi-square or Fisher’s exact tests for categorical variables and parametric or non-parametric tests for continuous variables based on data distribution. We will use log-binomial regression to estimate risk ratios (RR) and 95% confidence intervals for the primary and secondary outcomes. While we anticipate that randomization will balance the distribution of measured and unmeasured potential confounders in the two study arms, if this is not the case, we will assess the influence of potential confounders as needed. In addition, we will perform pre-specified subgroup analysis among participants with ≤2 versus 3–5 zygotes on p.f.d 1, as well as participants with poor versus good quality embryos undergoing single embryo transfer. We will base analyses of the heterogeneity of treatment effects for these subgroups on a statistical test for interaction [18, 19]. This interaction test examines the extent to which any observed difference across subgroups may be attributed to chance variation. All data will be analyzed with SAS 9.4 (SAS Institute Inc., Cary, NC, USA).

The primary outcome of the trial is the live birth rate (≥ 22 weeks of gestation) per retrieval among poorer prognosis participants who have a cleavage stage embryo transfer compared with a blastocyst transfer in an intent-to-treat analysis. The intention-to-treat population will include all randomized participants, including those who cross over to the other treatment group (i.e. participants who are randomized to the blastocyst transfer group but in fact receive a cleavage-stage embryo transfer or participants in the cleavage-stage group who request a blastocyst transfer). Assuming a 25% live birth rate for cleavage stage transfer, a 10% absolute difference in live birth rate between blastocyst and cleavage-stage embryo transfer corresponds to a RR of 0.6 (RR = 0.15/0.25) (Fig. 3). The primary analyses will therefore be interpreted as follows: If the lower bound of the 95% confidence interval (CI) for the difference in live birth rates per retrieval lies to the right of the 10% non-inferiority margin (RR = 0.6), we will have proven non-inferiority of blastocyst transfers at the level of significance α = 0.025; superiority will be demonstrated if the lower bound of the two-sided 95% CI lies fully to the right of 1.0. If the whole 95% CI lies below the non-inferiority margin (RR = 0.6) for the outcome difference the treatment group will be declared “inferior.” If the 95% CI includes the RR = 0.6 noninferiority margin the study results will be deemed inconclusive (Fig. 3) [20].

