### Randomization

Embryos will be assessed on day 1 following egg retrieval, in accordance with usual clinical practice. If patients have 1 to ≤5 embryos with 2 pronuclei available, they will be randomized to receive a cleavage- or blastocyst -stage embryo transfer. We will use computer-generated block randomization to randomize participants in a 1:1 ratio to the day 3 or day 5 treatment arm. Randomization will be stratified based on treatment center, age (< 38 and ≥ 38 years) and by embryo number (1–2 and 3–5 embryos on day 1 after egg retrieval). Randomization will be performed electronically using a secure web application (REDCap). Allocation concealment will be ensured, as randomization will not occur until the patient becomes eligible to participate in the trial, which takes place after consent to participate. In addition, randomization will be performed by embryology lab personnel and not recruiting study physicians. As per standard clinical practice, a clinician (who also is a member of the study team) will call participants to inform them of the number of fertilized embryos and, at this point, will also inform them of the day of transfer to which they have been randomized. At this point, participants will have an opportunity to not continue with the day of transfer to which they were randomized. We anticipate that most of the crossovers will occur due to participants in the p.f.d. 5 group with only 1–2 embryos wishing to have an embryo transfer on p.f.d. 3. Participants who choose to not continue with their assigned day of transfer will be asked to continue their participation so that we can collect cycle outcome data for the intention-to-treat analysis. Due to the nature of the intervention neither participants nor staff can be blinded to allocation, but are strongly inculcated not to disclose the allocation status of the participant at the follow up assessments. An employee at Boston IVF outside the research team will feed data into the computer in separate datasheets so that the researchers can analyze data without having access to information about the allocation. Trial conduct and protocol adherence will be audited every 6 months by the clinical director of each individual study site.

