Our choice of a non-inferiority margin, i.e. the largest clinical difference in the live birth rate per retrieval that is acceptable between cleavage- and blastocyst-stage embryo transfer, is based on a combination of clinical judgment and statistical reasoning. Given that there are no data from previous trials to help define the clinical difference between cleavage-stage and blastocyst transfers in poorer prognosis patients, we have relied on our own and outside experts’ clinical judgment to determine that a non-inferiority margin of 10% is clinically acceptable. We used data from Boston IVF to estimate the live birth rate per transfer for cleavage-stage embryos. Among women with ≤5 zygotes on day 1, approximately 24% achieved a live birth after a day 3 transfer. Given that many of these cycles will not result in cryopreservation of embryos and subsequent frozen embryo transfer, it is reasonable to assume a live birth rate per cycle of approximately 25% for p.f.d. 3 transfers. Assuming a 25% live birth rate in both groups, a non-inferiority margin of 10%, a one-sided significance level of 0.025, and 80% power, a sample size of 296 per group is required. To allow for up to 10% of patients to withdraw from the study after randomization or be lost to follow-up, we aim to enroll 329 participants per group, yielding a total sample size of 658 participants. We estimate that there were 710 eligible patients in 2018 across all sites. Assuming 50% of eligible patients will consent to study participation, we anticipate an enrollment period of 22 months. Given that patients store their frozen embryos at our facilities we expect minimal loss to follow-up.

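### Non-inferiority is decided on intention-to-treat alone although mostly one-way crossover to cleavage transfer is expected, and an unadjusted per-protocol analysis may not reveal the resulting dilution

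*Protocol article*

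**What the plan says.** Under Data collection and statistical analysis, the article chooses the primary analysis with the words "we will perform an intention-to-treat analysis because it is the gold standard for RCTs, even with crossover, withdraw and loss to follow-up". The same section keeps crossovers in their randomised arm, naming "participants who are randomized to the blastocyst transfer group but in fact receive a cleavage-stage embryo transfer" and also cleavage-arm women who ask for a blastocyst transfer. The rule for declaring non-inferiority is attached to this intention-to-treat comparison. The other analysis is described as a "per-protocol analysis as it is a valid statistical approach and will serve as a sensitivity analysis". Nothing requires it to agree before non-inferiority is claimed.

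Under Randomization, women learn their allocation and may then decline the assigned day. The authors anticipate that "most of the crossovers will occur due to participants in the p.f.d. 5 group with only 1–2 embryos" who prefer a day-3 transfer. Women who decline are asked to stay in follow-up.

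The sample size section states that with "a one-sided significance level of 0.025, and 80% power, a sample size of 296 per group is required", and raises this to 329 per group for withdrawal and loss to follow-up. Crossover is not part of that allowance.

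**The concern.** In a superiority trial, crossover works against the claim, so intention-to-treat is the cautious choice. In a non-inferiority trial it works for the claim: women assigned to blastocyst who receive the control treatment pull the two arms together. The plan forecasts this pattern and then relies on the superiority-style argument.

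The usual safeguard is a per-protocol analysis. Here the expected crossovers are not a random sample: they come mainly from the 1–2 embryo group of one arm. The article lists embryo number among the factors that define prognosis (Background), says the risk of having nothing to transfer grows as embryo number falls (Study design and setting), and stratifies randomisation on it. If women with 1–2 zygotes have fewer live births, removing them mainly from the blastocyst arm raises that arm's rate. Both analyses could then lean the same way, and their agreement would reassure more than it should.

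**Working it through.** **1. The plan's own figure.** Inputs from the sample size section: 25% live birth in both arms, margin 10 points, one-sided 0.025, power 80%.

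n = (1.960 + 0.842)² × 2 × 0.25 × 0.75 / 0.10² = 294.3, so 295 per group against 296 stated. Then 296/0.90 = 328.9, so 329 per group and 658 in total. The arithmetic is sound.

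**2. Dilution of intention-to-treat.** True rates are set at the margin: cleavage 25%, blastocyst 15%. A share c of the blastocyst arm crosses to cleavage. The documents give no c, so 5–20% is an assumption. Two cases:

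- Average crossovers: each moves from 15% to 25%, so the arm's rate is 0.15 + 0.10c.
- Poorer-prognosis crossovers: cleavage rate a = 12–15% and blastocyst rate 0.6a (the plan's margin ratio), so the arm's rate is 0.15 + 0.4ac.

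Probability that the lower 95% limit of the difference exceeds −10 points, by exact enumeration at 329 per arm:

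| c | Rate, average crossovers | False non-inferiority | Rate, poorer prognosis | False non-inferiority |
|---|---|---|---|---|
| 0 | 15.0% | 2.6% | 15.0% | 2.6% |
| 5% | 15.5% | 3.7% | 15.2–15.3% | 3.0–3.2% |
| 10% | 16.0% | 5.1% | 15.5–15.6% | 3.6–3.9% |
| 15% | 16.5% | 7.0% | 15.7–15.9% | 4.3–4.8% |
| 20% | 17.0% | 9.3% | 16.0–16.2% | 5.0–5.8% |

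**3. Unadjusted per-protocol, crossovers dropped.** Let s be the share of women with 1–2 zygotes, f the fraction of them crossing over, and a and b the live birth rates with 1–2 and 3–5 zygotes. After dropping, the 1–2 zygote share of the blastocyst arm is w = s(1 − f)/(1 − sf). With no true effect, the shift in favour of blastocyst is (s − w)(b − a). Assumed ranges: s 35–40%, a 12–15%, b 30–32%, f 20–50%.

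- Smallest: s = 0.35, f = 0.20, a = 0.15, b = 0.30. w = 0.28/0.93 = 0.301; shift = 0.049 × 0.15 = +0.7 points.
- Largest: s = 0.40, f = 0.50, a = 0.12, b = 0.32. w = 0.20/0.80 = 0.25; shift = 0.15 × 0.20 = +3.0 points.
- Equal rates (a = b): shift 0.

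At the margin, take s = 0.40, f = 0.50, a = 0.15 and risk ratio 0.6 in both zygote groups. To give 25% overall, b = (0.25 − 0.40 × 0.15)/0.60 = 0.317. The blastocyst per-protocol rate is 0.6 × (0.25 × 0.15 + 0.75 × 0.317) = 16.5%, a difference of −8.5 points instead of −10. False non-inferiority is about 6.3% (normal approximation, 296 per group before exclusions). With a = 25% it returns to 2.5%. With a = 30% the bias reverses: −10.75 points and 1.5%.

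**4. Power of a complier-average criterion.** SE = √(2 × 0.1875/296)/(1 − c) = 0.0356/(1 − c), and power = Φ(0.10/SE − 1.96). This gives 80% at c = 0, then 76%, 72% and 67% at 5%, 10% and 15% crossover.

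**The case against.** The strongest reply is that intention-to-treat answers the question the trial asks. The Background closes by stating the primary aim in terms of women randomised to each strategy, and the Discussion calls the trial pragmatic. For that policy question the analysis is unbiased and its 2.5% stands. A reader might infer that the error rate simply fails, and the documents do not support that. However, the Aim section and the statement of the primary outcome are worded by the transfer itself, and the abstract looks ahead to uniform blastocyst culture. Under uniform culture, opting out to day 3 would not be on offer, so the effect of the transfer also matters.

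A reader might also take crossover as strictly one-way. The article says only that most will go in that direction, and it provides for the reverse. Reverse crossover also dilutes intention-to-treat, but it makes the per-protocol exclusions less one-sided.

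The upper ends of the two illustrations should not be combined. The 9.3% treats crossovers as average women, whereas the per-protocol shift needs them to have a poorer prognosis. With poorer-prognosis crossovers the intention-to-treat risk at 20% crossover is 5.0–5.8%.

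It is tempting to say that both analyses are certain to be biased the same way. That needs live birth rates by zygote number, which the documents do not give. Nor can it be said that the per-protocol set drops women whose embryos arrested: the article does not define the set, and a condensed article may leave the definition and any adjustment to the analysis plan.

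Some mitigation exists. Women whose treatment plan prefers either day are excluded, counselling addresses the fear of having nothing to transfer, and a subgroup analysis by zygote number with an interaction test is planned. These may lower crossover or give partial insight, but they do not change the decision rule.

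**Conclusion.** The point stands in this limited form. The article fixes a non-inferiority rule on intention-to-treat alone while forecasting crossover that favours the claim. For the effect of the transfer, the risk of a false claim exceeds 2.5%: about 3.6–5.1% at 10% crossover and 5.0–9.3% at 20%. These ranges assume 329 per arm, true rates of 25% and 15%, and the difference scale. The direction follows from the documents; the size depends on a crossover rate they do not state.

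The per-protocol analysis may fail to show the problem if it is unadjusted and if women with 1–2 zygotes do worse. The documents suggest the second condition by treating embryo number as prognostic, but they do not quantify it. For the effect of assignment, intention-to-treat remains valid.

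**What to change.** Keep intention-to-treat as the primary analysis. Add to the decision rule that non-inferiority is claimed only if a per-protocol analysis, stratified or adjusted by zygote number, age and centre, supports it. Define that set so that blastocyst-assigned women who have no embryo to transfer remain in it as adherent, with no live birth. Adjustment removes only the part of the selection explained by these factors, which should be said when the result is reported.

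Also report a complier-average difference, with randomisation as the instrument, as a supportive sensitivity analysis. State that it applies to compliers. It should not be a mandatory co-criterion: alone it would have about 76%, 72% and 67% power at 5%, 10% and 15% crossover with 296 evaluable per arm, against 80% for intention-to-treat.

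The cost is a change of wording, the additional analysis, and some loss of power for the joint claim. No new data are needed, because women who decline their assigned day are already asked to remain in follow-up.

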A recent Cochrane meta-analysis of 27 randomized controlled trials (RCTs) by Glujovsky et al. found a higher live birth rate, per transfer, in the fresh blastocyst transfer group compared to cleavage-stage transfer (odds ratio (OR) 1.48, 95% confidence interval (CI) 1.20 to 1.82) and no evidence for a difference in the rates of miscarriage, multiple pregnancies, and high-order multiples [1]. However, this analysis only included 539 patients and was not powered to identify subgroups of patients who may benefit from a cleavage-stage transfer. In addition, because of attrition during culture to the blastocyst stage in vitro, the live birth rate should be evaluated per retrieval, rather than per transfer. Based on individual RCTs, the best evidence for an increased likelihood of live birth after transfer of fresh blastocysts compared with cleavage-stage embryos exists in good prognosis patients (defined by such factors as age, number of previous failed attempts, ovarian response, and number and quality of embryos) [1–6]. As a result, there now is a general consensus that, for good prognosis patients, it is beneficial to transfer a blastocyst rather than a cleavage stage embryo. However, in unselected patients, RCTs have yielded conflicting results, and in poorer prognosis patients no high-quality studies have evaluated whether the live birth rate is higher with fresh blastocyst or cleavage-stage transfer [1, 7]. Thus, at present, many providers offer a p.f.d 3 transfer to patients with few available embryos to reduce the incidence of cycle cancellation due to failure of embryo development to the blastocyst stage. At our center, this approach is offered to patients with ≤5 zygotes on day 1 after fertilization and as a result 35% of all patients receive a p.f.d 3 embryo transfer, which is consistent with national trends.

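### Randomisation is stratified by centre, age and zygote number, but the only stated covariate rule is adjustment for observed imbalance, which would rarely admit those factors and leaves the deciding estimate open

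*Protocol article*

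**What the plan says.** Protocol article, Randomization: "Randomization will be stratified based on treatment center, age (< 38 and ≥ 38 years) and by embryo number". The age cut is 38 years, the zygote groups are 1–2 and 3–5, and allocation is 1:1 in computer-generated blocks.

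Protocol article, Data collection and statistical analysis: "We will use log-binomial regression to estimate risk ratios (RR) and 95% confidence intervals for the primary and secondary outcomes". No covariates or strata are named. Randomisation is expected to balance confounders, and "if this is not the case, we will assess the influence of potential confounders as needed". No covariate list or criterion for imbalance is given. Zygote number returns in this section only as a subgroup factor, tested by interaction.

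The later paragraph that sets the decision rule compares the lower limit of the 95% confidence interval with the margin. It mentions neither strata nor adjustment.

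The Background treats good prognosis as "defined by such factors as age, number of previous failed attempts, ovarian response, and number and quality of embryos", so the article itself regards age and embryo number as prognostic.

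**The concern.** Stratified randomisation removes chance differences between the arms on the stratification factors. If those factors predict live birth, a standard error that ignores them still counts variation that the design has taken out, and the interval is wider than it needs to be. Including the strata recovers that precision.

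A rule triggered by imbalance works against this. It leaves out the factors that were balanced on purpose and admits others that happen to differ by chance. Since neither the list nor the threshold is fixed, more than one estimate could claim to be primary.

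At stake is the reading of a borderline result. The trial turns on one confidence limit, and an interval that includes the margin is declared inconclusive. Two admissible limits on either side of the margin would leave the conclusion open to dispute.

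**Working it through.** **1. The plan's own figure.** The sample size section takes the live birth rate as 25% in each arm. The other inputs and the result are given there as: "a non-inferiority margin of 10%, a one-sided significance level of 0.025, and 80% power, a sample size of 296 per group is required".

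n = 2 × 0.25 × 0.75 × (1.960 + 0.842)² / 0.10² = 294.3, so 295 against the stated 296. Allowing for 10% loss, 296 / 0.90 = 328.9, so 329 per group and 658 in total. The figures reproduce.

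At 296 per group the standard error is √(2 × 0.25 × 0.75 / 296) = 0.0356. The 95% half-width is 7.0 points and power is Φ(0.10/0.0356 − 1.96) = 80%.

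**2. What the strata could add.** The article gives no stratum rates, so all rates and weights below are assumptions. The four strata are age group by zygote group, in descending order of assumed live birth rate. Centre is left out.

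- μ = Σ w·p, and R² = Σ w(p − μ)² / [μ(1 − μ)]
- SE without strata = √(2μ(1 − μ)/296); SE with strata = SE × √(1 − R²)
- Power with strata = Φ(0.10/SE_with − 1.96)
- Power without strata = Φ((0.10 − 1.96 × SE_without)/SE_with), because the true sampling error under stratified allocation is the smaller one
- One-sided error without strata = 1 − Φ(1.96/√(1 − R²))

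Example for scenario A: μ = 0.248, between-stratum variance 0.0092, total variance 0.1865, R² = 0.0092/0.1865 = 0.049, √(1 − 0.049) = 0.975.

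| Scenario | Rates (%) | Weights (%) | R² | Adjusted CI narrower by | Power without → with strata | One-sided error without strata |
|---|---|---|---|---|---|---|
| A | 38/25/20/12 | 30/20/30/20 | 0.049 | 2.5% | 81.0 → 82.4% | 2.2% |
| B | 42/24/22/8 | 30/20/30/20 | 0.077 | 3.9% | 80.6 → 82.7% | 2.1% |
| Mild | 32/26/22/16 | 35/15/30/20 | 0.019 | 1.0% | 80.6 → 81.1% | 2.4% |
| Moderate | 38/26/18/10 | 35/15/30/20 | 0.064 | 3.3% | 81.4 → 83.1% | 2.1% |
| Strong | 45/25/13/5 | 35/15/30/20 | 0.142 | 7.4% | 82.7 → 86.4% | 1.7% |

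With equal rates in all strata, R² = 0 and nothing changes.

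**3. Simulation check.** This used 40,000 trials per scenario, about 296 per arm, with arms balanced within strata and equal true rates. Coverage of the unadjusted 95% interval was 95.2%, 95.5% and 96.5% in the mild, moderate and strong scenarios. Coverage of the stratified interval was 94.9%, 94.6% and 94.8%. Risk-difference power rose from 80.7 to 81.4%, 81.2 to 83.1% and 82.9 to 86.8%, in line with the table.

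**4. The rule beside the design.** The condition for considering covariates is that randomisation has not balanced the arms. Age group, zygote group and centre are the variables that randomisation forces towards balance. Followed as written, the rule rarely reaches them.

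**The case against.** The article never calls the primary model unadjusted. It names no covariates in or out, and a condensed article may leave the list to a fuller plan. A reader might infer that the strata are deliberately ignored, but the text does not support that. The imbalance rule, however, is written out, and a fuller plan that fixed the strata would have to override it.

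Assessing the influence of confounders may mean a robustness check. A reader might infer that the primary model will be chosen from the data, but the article does not say so, and it has researchers analyse without access to allocation, which limits such a choice. What stands is that the status of the adjusted result is not stated, although the per-protocol analysis in the same section is plainly labelled as sensitivity.

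The power argument can be overstated. The 80% applies to 296 per group. The plan enrols 329 and expects little loss to follow-up. With all 329 analysed and 25% in both arms, SE = √(0.375/329) = 0.0338 and unadjusted power is Φ(0.10/0.0338 − 1.96) = 84%. On the risk-ratio scale against 0.6, SE(log RR) = √(2 × 3/296) = 0.142 and power is Φ(0.511/0.142 − 1.96) = 95%. In the simulation, adjustment added only about 0.2–1.3 points there. This stands and keeps the point modest.

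**Conclusion.** The point holds in a limited form. The plan stratifies on factors that it regards as prognostic, names none of them in the primary analysis, and states a covariate rule that would rarely admit them. It does not fix which estimate meets the margin.

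The loss of precision is small: intervals about 1–7% narrower with adjustment (2.5–3.9% in scenarios A and B), and about 0.5–4 points of risk-difference power at 296 per group (about 81% to 82–83% in A and B). These sizes rest on assumed stratum rates and leave out centre.

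A reader might infer that an analysis without the strata is invalid or could produce a false claim of non-inferiority. The calculation shows the reverse: one-sided error falls below 2.5%, to about 1.7–2.4%. The design and the sample size stand. The undefined primary estimate matters whatever the size of the precision gain.

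**What to change.** Pre-specify one primary intention-to-treat estimate, adjusted for age group, zygote group and centre, and state that its confidence limit is the one compared with the margin. A stratified Mantel-Haenszel risk difference would serve, as would logistic regression with standardisation. The latter also avoids possible non-convergence of a log-binomial model with several covariates.

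If each of the 6 centres is a stratum, there are 6 × 2 × 2 = 24 cells. That is about 658/24 = 27 participants and, at 25%, about 7 live births per cell. The method should therefore tolerate sparse strata, or the factors should enter as main effects.

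Replace the imbalance-triggered sentence with a statement that any further covariate model is a sensitivity analysis.

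The cost is wording only. All three factors are already recorded at randomisation, and no additional participants are needed.

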**Fig. 3 Fig3:**
[figure not shown]
Possible outcomes of the PRECiSE non-inferiority RCT. The non-inferiority margin is set to a 10% absolute difference in live birth rate, which corresponds to a risk ratio (RR) of 0.6 for p.f.d 5 versus p.f.d.3 embryo transfer. **a** the lower bound of the confidence interval (CI) lies above the non-inferiority margin of 0.6: p.f.d. 5 is non-inferior to p.f.d. 3 embryo transfer (**b**) the lower bound of the CI lies above the non-inferiority margin and the CI includes the null value (RR = 1.0): p.f.d. 5 is non-inferior and equivalent to p.f.d. 3 embryo transfer (**c**) and (**d**) the CI includes the non-inferiority margin of 0.6: inconclusive (**e**) the upper bound of the CI lies below the non-inferiority margin of 0.6: p.f.d. 5 is inferior to p.f.d. 3 embryo transfer (**f**) the lower bound of the CI lies above the null value (RR = 1.0): p.f.d. 5 is superior to p.f.d. 3 embryo transfer

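### The non-inferiority margin is justified and sized as a 10-point difference but judged as a fixed risk ratio of 0.6, and the plan does not say which scale governs

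*Protocol article*

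**What the plan says.** The section on the rationale for the non-inferiority hypothesis and sample size relies on clinical judgement that "a non-inferiority margin of 10% is clinically acceptable", and sizes the trial on that absolute figure: "Assuming a 25% live birth rate in both groups, a non-inferiority margin of 10%, a one-sided significance level of 0.025, and 80% power". The result is 296 per group, raised to 329 per group for 10% loss.

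The section on data collection and statistical analysis names one estimator: "We will use log-binomial regression to estimate risk ratios (RR) and 95% confidence intervals for the primary and secondary outcomes". It converts the margin to a risk ratio by dividing 0.15 by 0.25, on the stated assumption of a 25% cleavage-stage rate. The rule for non-inferiority then concerns the interval "for the difference in live birth rates per retrieval lies to the right of the 10% non-inferiority margin", with the ratio of 0.6 in brackets after it. Superiority is read against 1.0, and inferiority and inconclusive results against 0.6.

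The Fig. 3 caption joins the two scales again: "The non-inferiority margin is set to a 10% absolute difference in live birth rate, which corresponds to a risk ratio (RR) of 0.6". It reads all of its outcomes, a to f, on the ratio scale.

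**The concern.** A 10-point loss and a risk ratio of 0.6 are the same margin at one control rate only. The text that defends the margin and fixes the sample size uses points. The text that estimates the effect and declares the result uses a ratio, except that the sentence defining non-inferiority names a difference. Two analysts could follow this plan in good faith and report different primary conclusions from the same data.

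Two things are at stake. First, the governing scale could be settled after the results are known, in a trial where neither participants nor staff can be blinded to allocation. Second, if the ratio governs and the cleavage rate is above 25%, the loss that the trial tolerates exceeds the one judged clinically acceptable.

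**Working it through.** **Inputs from the protocol article.** Margin 10 points; 25% live birth in both arms; one-sided level 0.025; power 80%; 296 per arm (329 with allowance for loss); 1:1 allocation; ratio threshold 0.6.

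**Assumptions made here.** Wald 95% interval for the difference; Wald interval on the log risk ratio, which is what an unadjusted log-binomial model gives. Control rates other than 25% are not in the document and are shown as a range. Probabilities come from exact enumeration of the binomial outcomes.

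**1. The plan's own sample size.** On the difference scale, n = (1.96 + 0.8416)² × 2 × 0.25 × 0.75 / 0.10² = 294.3 per arm. With the Farrington-Manning null variance it is 295.1, rounded up to 296. Then 296 / 0.90 = 328.9, so 329 per arm and 658 in total. The stated figures are reproduced.

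On the ratio scale, n = (1.96 + 0.8416)² × 2 × (0.75/0.25) / (ln 0.6)² = 180.5, so 181 per arm. The stated 296 at 80% power therefore belongs to the difference rule only.

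**2. What a ratio of 0.6 allows.** The tolerated loss is 0.4 × the control rate: 8 points at 20%, 10 at 25%, 12 at 30%, 14 at 35%.

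**3. One dataset under both rules.** Take cleavage 74/296 (25.0%) and blastocyst 61/296 (20.6%).
- Difference: −4.4 points. SE = √(0.25 × 0.75/296 + 0.206 × 0.794/296) = 0.0344. CI −11.1 to +2.4 points. It contains −10, so the result is inconclusive.
- Ratio: 61/74 = 0.824. SE of the log = √(1/61 − 1/296 + 1/74 − 1/296) = 0.152. CI 0.61 to 1.11. The lower limit exceeds 0.6, so the result is non-inferior.

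With 74 cleavage births, every blastocyst count from 60 to 64 splits the rules in this way. The observed control rate is exactly 25% here, so the split comes from the different widths of the two intervals and not from a wrong planning rate.

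The split can also run the other way. For 44/296 against 38/296, the difference CI is −7.6 to +3.5 points (non-inferior) and the ratio CI is 0.577 to 1.292 (inconclusive).

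**4. Operating characteristics, 296 per arm.**

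| Control rate | Power, equal arms: difference / ratio | Rules disagree, equal arms | Accepts a true 10-point loss: difference / ratio |
|---|---|---|---|
| 20% | 86.1% / 86.8% | 4.5% | 2.7% / 0.2% |
| 25% (planned) | 80.4% / 94.4% | 14.0% | 2.6% / 2.6% |
| 27% | 78.4% / 96.1% | 17.8% | 2.5% / 5.2% |
| 30% | 75.7% / 97.9% | 22.2% | 2.5% / 11.3% |
| 35% | 72.2% / 99.4% | 27.2% | 2.5% / 27.9% |

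At 329 per arm and 25%, power is 84.3% and 96.1%, and the rules disagree in 11.9% of trials.

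**The case against.** The best defence is that there is one rule, on the ratio scale, loosely worded. The conversion states its condition of a 25% cleavage rate. The estimator, the superiority, inferiority and inconclusive rules, and all of Fig. 3 use the ratio. A risk ratio is a legitimate scale for non-inferiority, and at the planned rate its power is above the stated 80% with error near 2.6%. This reading is possible, but it does not clear the plan. The sentence that defines non-inferiority still names a difference. The margin has no justification as a ratio, and the stated power is not that of the ratio rule.

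Three stronger readings are tempting, and the documents do not support them.

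- A reader might infer that the two rules give opposite verdicts. Under the protocol's own categories the disagreement is non-inferior against inconclusive. The chance that one rule says non-inferior while the other says inferior is below 0.00001 at every control rate checked from 20% to 40%.
- A reader might cite 104/296 against 80/296 as significantly worse on one scale and non-inferior on the other. The difference CI (−15.5 to −0.7 points) contains −10 and so is inconclusive. The ratio CI (0.603 to 0.981) excludes 1 as well. A result that is worse than control but within the margin can occur under any margin.
- A reader might infer that the error rate is inflated as planned. At 25% it is not, and below 25% the ratio rule is the stricter one. The document gives 24% per transfer and about 25% per cycle for cleavage transfer. Its 38% is a per-transfer rate for blastocysts and does not support a control rate in that region.

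**Conclusion.** The concern holds as an inconsistency in the stated primary decision rule. It is not a detail that an analysis plan could be left to supply, because the article itself states the rule and puts both scales in it.

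The part that rests on the plan's own figures is the 14-point gap in power and the disagreement in 14.0% of trials at 296 per arm (11.9% at 329) with 25% in both arms. The loss of error control depends on a control rate above 25%. It is modest close to the plan (5.2% at 27%) and large only at assumed rates of 30% or more. The exact figures rest on unadjusted Wald intervals; an adjusted analysis would shift them somewhat.

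This should be settled before any outcome data are compared, because the primary conclusion can turn on it.

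**What to change.** Name one governing scale. The risk difference is the one that fits the stated justification and 296 per arm at 80% power:

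- non-inferior if the lower limit of the two-sided 95% CI for blastocyst minus cleavage is above −10 points;
- superior if that limit is above 0;
- inferior if the upper limit is below −10 points;
- inconclusive otherwise.

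State the method for this interval, redraw Fig. 3 on the same scale, and report the risk ratio as supportive without 0.6 as a threshold.

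If the sponsor prefers a ratio of 0.6, that is open to it. It should then justify the margin as a ratio, including the absolute loss that this allows at control rates other than 25%, restate the power, and remove the references to a difference from the rule.

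The cost of the first option is wording and one figure, with no more patients. The price is that power at the design point is the stated 80% and not the roughly 94% of the ratio rule, and that it falls if the control rate is higher (75.7% at 30%).
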